## Abstract

**Background:**

Tuberculosis is an infectious disease that continues to cause considerable morbidity and mortality globally. Only 65% of patients worldwide are currently diagnosed. Contact investigation is a strategy that aims to increase case detection and reduce transmission of tuberculosis, yet there is little evidence to show its effectiveness.

**Methods/Design:**

We will conduct a cluster randomized controlled trial of contact investigation within the national tuberculosis control program of Vietnam. Household contacts of patients with smear-positive pulmonary tuberculosis will be invited to attend district tuberculosis units for symptom screening, examination, and chest radiography on four occasions over a two-year period. The primary endpoint is clinically confirmed tuberculosis among contacts during the 24 months of follow-up, ascertained using capture-recapture analysis. Microbiologically proven tuberculosis and treatment completion rates among contacts diagnosed with tuberculosis will be secondary endpoints. The incremental cost-effectiveness ratio will be estimated. The study will have 80% power to detect a 50% increase in the primary endpoint in the active intervention arm compared with the control arm. The study will include 8,829 contacts in each of the active screening and control groups, within 70 districts in 8 provinces in Vietnam, in both rural and urban settings.

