### Hypothesis and aims

The hypothesis of this study is that, in countries that are highly endemic for TB, targeted active case finding among household contacts will result in more contacts being diagnosed with TB than will standard passive case finding alone.

The primary aim of the study is to determine if household contact investigation is effective, by determining whether it increases the overall yield of active TB diagnosed among household contacts of patients with smear-positive TB compared with usual passive case detection. There are two secondary aims. The first is to estimate the cost effectiveness of this intervention by measuring the incremental cost-effectiveness ratio. The second is to determine the feasibility of implementing contact investigation within the NTP in a range of settings in Vietnam, including urban and rural environments. The screening strategy proposed in this study will be operationally nested within the NTP.

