### Study endpoints

The following endpoints are being measured in all contacts (in both groups). The primary endpoint is the proportion of contacts with clinically diagnosed TB. This will be ascertained based on the results of screening (in the active screening districts) and routine notifications to the NTP (in the active screening and control districts). Secondary endpoints, as indirect measures of study feasibility, are: (a) the weighted proportion of contacts with microbiologically proven TB (defined as either smear or culture positive TB), smear-positive TB and extrapulmonary TB; (b) cost effectiveness, determined by calculating the direct and indirect costs for each additional case diagnosed; and (c) the proportion of eligible contacts enrolling in the study, and the proportion of contacts participating in scheduled follow-up.

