### Control districts

Contacts enrolled in control districts, will be given general information about the typical symptoms of TB and advised to report to the district hospital or TB unit if they develop these symptoms. During the study period, self-referring contacts with TB, who are participating in the study, will have two sputum specimens transferred to the reference laboratory for culture, in addition to any routine diagnostic procedures. This will allow comparison of rates of culture-confirmed TB between active and control districts. Contacts diagnosed with TB in both the control and active intervention groups will receive standard treatment for TB through the NTP.

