### Analysis of effectiveness

The effectiveness of the active case finding in contacts will be assessed by comparing the case detection rate between contacts of index cases in the active intervention and control districts. There are two levels of clustering in the selection of contacts: the district in which the contact lives and the index case with whom he or she was in contact. To account for these two levels of clustering, we will undertake a mixed model analysis in which districts and index cases within districts are random effects and active versus control status is the fixed effect. The measure of effect will be relative risk, estimated using a log link and binomial error distribution. In this primary analysis, there will be no adjustment for baseline characteristics. However, in a subsidiary analysis we will examine the impact of baseline characteristics of the districts, including geographical characteristics and baseline case notification rate, and individuals, including age and sex, on the risk of disease by testing these characteristics as potential effect modifiers.

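### The abstract ascertains the primary endpoint by capture-recapture, but the body defines and models observed diagnoses and lists only one case source for control districts

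*Protocol article*

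**What the plan says.** The protocol article describes the primary endpoint in three places.

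- **Abstract, Methods/Design:** "The primary endpoint is clinically confirmed tuberculosis among contacts during the 24 months of follow-up, ascertained using capture-recapture analysis". The same paragraph gives 80% power for a 50% increase in that endpoint, with 8,829 contacts per group.
- **Study endpoints:** "The primary endpoint is the proportion of contacts with clinically diagnosed TB". On sources: "This will be ascertained based on the results of screening (in the active screening districts) and routine notifications to the NTP". The second source is "routine notifications to the NTP (in the active screening and control districts").
- **Primary and secondary endpoints and stratification:** a weighted proportion of contacts clinically diagnosed over two years.

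Hypothesis and aims asks "whether it increases the overall yield of active TB diagnosed among household contacts". Analysis of effectiveness proposes "comparing the case detection rate between contacts of index cases in the active intervention and control districts", as a relative risk from a model with log link, binomial error, and random effects for district and for index case within district. Under Control districts, contacts are "advised to report to the district hospital or TB unit if they develop these symptoms"; no scheduled screening takes place there.

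**The concern.** Capture-recapture does not count recorded cases. It uses the overlap between two or more lists to estimate how many cases exist in all, including those on no list. The abstract and the body therefore name different quantities as the primary endpoint.

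Three things are at stake. First, the method needs overlapping lists, and the listed sources differ by arm. Second, an estimate of all TB is not the yield of diagnosed TB that the trial sets out to compare. Third, the method returns a group total, whereas the binomial mixed model needs a yes/no outcome for each contact. An analyst who followed the abstract could not fit the model in the body, and the answer would depend on which arms were corrected.

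**Working it through.** **1. The plan's own sample size, and which endpoint it supports.** Inputs from Sample size calculation: 2.3%, a 50% relative increase, 80% power. Two-sided alpha of 0.05 is assumed, as it is not stated. With p1 = 0.023, p2 = 0.0345 and mean 0.02875:

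n = [1.960 × √(2 × 0.02875 × 0.97125) + 0.842 × √(0.023 × 0.977 + 0.0345 × 0.9655)]² / 0.0115² = (0.4632 + 0.1988)² / 0.00013225 ≈ 3,313.3.

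The plan states 3,313. Clustering: 1.3 × 2.05 = 2.665, and 3,313 × 2.665 = 8,829, as stated. This is a comparison of two observed proportions of contacts. It agrees with the body's endpoint and has no capture-recapture component.

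**2. Case sources by arm (Study endpoints).**

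| Source | Active | Control |
|---|---|---|
| Study screening | yes | no |
| Programme notification | yes | yes |

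The two-list (Lincoln-Petersen) estimate is N = n1 × n2 / m, where m is the number of cases on both lists. In control districts, with only the notification list, n2 = 0 and m = 0, so N = 0/0 is undefined. The Chapman version gives (n1 + 1)(0 + 1)/(0 + 1) − 1 = n1, which is simply the observed count.

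In active districts the two lists are unlikely to be independent: contacts diagnosed at screening are treated through the national programme, so one list can feed the other.

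**3. Effect on the comparison.** Assume underlying TB is equal in the two arms, as randomisation should make it approximately. Let dA and dC be the fractions detected.

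- Observed diagnoses: ratio = dA / dC.
- Active arm fully corrected, control arm left as observed: ratio = 1 / dC, which is at least dA / dC because dA cannot exceed 1.
- Both arms fully corrected: ratio = 1.

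Illustration: the plan expects screening to find 75% of cases, 50% more than passive finding, so dC = 0.75 / 1.5 = 0.50. The ratios are then 0.75 / 0.50 = 1.5, 1 / 0.50 = 2.0 and 1.0.

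If the active arm is fully corrected and the control estimate reaches only a fraction c of true cases, the ratio is 1 / c. As c runs from 0.50 (no correction) to 1 (complete), the ratio runs from 2.0 to 1.0. The documents do not give c.

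**The case against.** The endpoint sections and the model already agree on diagnosed contacts, so the conflict comes from one clause in an abstract. That clause may be a loose way of saying that contacts are matched to the programme register. This limits the damage, but the wording would still be wrong, because matching and capture-recapture are different procedures.

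Several stronger readings are tempting, and the documents do not support them.

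- **That capture-recapture is impossible in the control arm.** Data collection and management has every district report study endpoints monthly, and under Control districts sputum from self-referring contacts goes to a reference laboratory. These records could become further lists, and a full protocol might say so. They are not described as independent or as used in this way, so the claim reaches only as far as the sources listed for the endpoint.
- **That the result would be null by construction.** This needs complete, homogeneous capture in both arms. Sample size calculation reports that about half of prevalent cases in the national survey lacked typical symptoms. Such people have little chance of entering any passive list, so a control estimate would probably fall short of the true total. Moreover, if both lists recorded diagnosed cases only, the method would correct under-recording of diagnoses, which is compatible with the yield aim.
- **That the bias can be put in case numbers.** Taking 2.3% as true prevalence gives 0.023 × 8,829 = 203 cases per arm. But 3,313 reproduces only with 2.3% as the control-arm proportion; halving it for passive detection (1.15% v 1.725%) gives 6,726 by the same formula. A baseline ratio of 1.75, from [1 − 0.25 × 0.50] / 0.50, also needs independent lists and departs from the planned 1.5.
- **That the case detection rate in Analysis of effectiveness needs an unobtainable count of all TB.** The comparison is between contacts, with a relative risk and binomial error, so contacts are the natural denominator.

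**Conclusion.** The point stands as a contradiction about the primary endpoint. The abstract names an ascertainment method that the body does not use, that the listed sources do not support in control districts, and whose usual target, total TB, does not match the aim or the per-contact model.

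The direction of error is clear in two cases, given equal underlying TB in the arms: correcting the active arm alone favours the intervention, and a valid correction of both arms for undetected disease pulls the ratio towards 1. The size is not determined. The span of 2.0 to 1.0 around a planned 1.5 is an illustration that rests on 50% passive detection and a fully corrected active arm.

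The definition in the body is workable and the sample size agrees with it. What needs correcting is the abstract's statement, and this should be settled before analysis.

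**What to change.** Delete the capture-recapture clause from the primary endpoint in the abstract. State instead that the endpoint is the proportion of enrolled contacts with a documented TB diagnosis within 24 months, from study screening records and programme notifications, with contacts matched to the programme register by the same procedure in both arms.

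If capture-recapture is wanted, present it as a descriptive check on completeness of ascertainment, outside the primary comparison, and name its lists and overlap for each arm.

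Cost: a wording change and a register-matching step for contacts. That step may be new work, since the registry check under Evaluation and monitoring covers index patients only. The trial would also make no claim about undetected cases. The sample size stays at 3,313 × 2.665 = 8,829 per group.

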### Primary and secondary endpoints and stratification

The primary endpoint will be the weighted proportion of contacts with clinically diagnosed TB in screening and control districts during the two-year follow-up period of the study. Secondary endpoints will include the weighted proportion of contacts with microbiologically proven TB, smear-positive TB, and extrapulmonary TB. We will also estimate the proportion of contacts with TB who complete treatment. Stratum specific weighted prevalence rates of clinically diagnosed and microbiologically proven TB will be determined for region and rurality.

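### The primary endpoint is stated in three ways that do not agree (capture-recapture, plain proportion, weighted proportion); the primary model and the sample size fit only the plain observed proportion

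*Protocol article*

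**What the plan says.** The protocol article describes the primary endpoint in three places.

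- **Abstract, Methods/Design:** clinically confirmed TB in contacts, "during the 24 months of follow-up, ascertained using capture-recapture analysis". Capture-recapture is not mentioned again in the article.
- **Study endpoints:** "The primary endpoint is the proportion of contacts with clinically diagnosed TB". Ascertainment is "based on the results of screening (in the active screening districts) and routine notifications to the NTP (in the active screening and control districts"). In this section the word weighted is attached only to secondary endpoints.
- **Primary and secondary endpoints and stratification:** "The primary endpoint will be the weighted proportion of contacts with clinically diagnosed TB in screening and control districts", over the two-year follow-up. The weights are not defined.

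Three other sections bear on which version is meant.

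- **Hypothesis and aims:** the primary aim is to determine whether contact investigation "increases the overall yield of active TB diagnosed among household contacts", compared with passive detection.
- **Analysis of effectiveness:** a mixed model with random effects for district and for index case within district. "The measure of effect will be relative risk, estimated using a log link and binomial error distribution". Neither weights nor a capture-recapture step is mentioned.
- **Sample size calculation:** 2.3% TB in contacts, about half of prevalent cases without typical symptoms, at least 75% found by screening, a 50% increase in detection, 3,313 contacts per group before clustering and 8,829 after.

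**The concern.** The three statements define different quantities. A plain proportion counts contacts who were diagnosed. A weighted proportion counts the same contacts but gives districts or individuals unequal influence. A capture-recapture estimate is a modelled total that includes cases appearing on no list.

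The third is the serious conflict. The trial asks whether screening leads to more contacts being diagnosed. An estimator that restores the undiagnosed cases estimates how much TB there is, which is the quantity expected to be the same in both arms. Used as the primary outcome, it would work against the question asked.

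The named sources add a second difficulty. Two-list capture-recapture needs two overlapping lists. Study endpoints names screening and notifications in active districts, but only notifications in control districts.

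At stake is which result decides the trial. As published, any of the three versions could later be called prespecified, and they need not agree.

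**Working it through.** **1. Which endpoint was powered?**

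Inputs from Sample size calculation: 2.3%, a 50% relative increase (so 3.45%) and 80% power. Alpha is not stated; two-sided 0.05 is assumed because it reproduces the stated figure.

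n = [z(0.975)·√(2·p̄·(1−p̄)) + z(0.80)·√(p1(1−p1) + p2(1−p2))]² / (p2−p1)², with p1 = 0.023, p2 = 0.0345 and p̄ = 0.02875

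= (0.46318 + 0.19877)² / 0.0115² = 0.43818 / 0.00013225 = 3,313.3

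The plan states 3,313, so the figure is reproduced.

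Clustering:
- households: 1 + (4−1) × 0.1 = 1.3
- districts: 1 + (106−1) × 0.01 = 2.05
- together: 1.3 × 2.05 = 2.665
- 3,313 × 2.665 = 8,829, as stated

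This is a comparison of two plain proportions. It has no term for weighting and none for the sampling error of a capture-recapture estimate. The powered endpoint is therefore the one in Study endpoints, although the Abstract claims the power for the endpoint it has just described by capture-recapture.

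**2. The statements side by side**

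| Section | Capture-recapture | Weighted | Observed diagnoses only |
|---|---|---|---|
| Abstract | yes | no | no, if used as an estimator |
| Study endpoints | no | no | yes |
| Primary and secondary endpoints and stratification | no | yes | yes |
| Analysis of effectiveness (model) | no | no | yes |
| Sample size calculation | no | no | yes |

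**3. What capture-recapture would do to the relative risk**

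This is an illustration with the sample-size inputs read as the text reads: 2.3% of contacts truly have TB, 50% of them are found passively and 75% in the active arm.

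- True cases per arm: 8,829 × 0.023 = 203
- Diagnosed, control: 203 × 0.50 = 102
- Diagnosed, active: 203 × 0.75 = 152
- Observed relative risk: 0.75 / 0.50 = 1.5

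The two-list estimate is N = A × B / m, where A and B are the list sizes and m is their overlap. If T true cases enter the two lists independently with probabilities s and r, the expected values give (T·s)(T·r)/(T·s·r) = T. The estimate returns the true total whatever the detection rates are. For example, s = r = 0.5 gives 1 − 0.5 × 0.5 = 75% observed, as in the active arm above, and an estimate of 203.

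| Use of capture-recapture | Active | Control | Relative risk |
|---|---|---|---|
| None (observed cases) | 152 | 102 | 1.5 |
| Both arms, working as intended | 203 | 203 | 1.0 |
| Active arm only | 203 | 102 | 2.0 |

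The ratios do not depend on the base rate. The stated 3,313 is in fact reproduced with 2.3% as the control-arm rate. On that reading the observed counts are 8,829 × 0.023 = 203 and 8,829 × 0.0345 = 305, the true total is 8,829 × 0.023/0.5 = 406, and the three ratios are again 1.5, 1.0 and 2.0.

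**The case against.** The strongest reply is that the plan already fixes the decisive comparison. Analysis of effectiveness specifies the model, the link, the random effects and the absence of baseline adjustment, and the sample size matches it. On this view the weighted proportions are descriptive estimates that follow from selecting districts in proportion to population, the Abstract phrase is loose, and list definitions and weights belong in a fuller document. Much of this is plausible, and it points to the right repair. It does not remove the contradiction: two sections still give the word primary to something the model does not estimate. Capture-recapture may have meant only cross-matching of records to count observed cases; the Abstract would then be mislabelled and still need correcting.

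Three stronger readings are tempting, and the documents do not support them.

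- *Capture-recapture is impossible in control districts.* Study endpoints names sources of ascertainment; it does not list capture-recapture lists. Under Data collection and management, every district reports study endpoints monthly, and under Control districts, specimens from self-referring contacts go to a reference laboratory. Neither is named as a list, and the cultures depend on the same self-referral as notification, so independence is doubtful. The limit is therefore conditional: it could not be applied alike unless a further list is defined.
- *The method inflates the effect.* Nothing says it would be used in one arm only. Used successfully in both arms, it would pull the relative risk towards 1.0.
- *Screening diagnoses count in the active arm without being registered.* This is not stated. Screening is done by programme staff, and diagnosed contacts in both arms are treated through the programme, so unregistered diagnoses may be few.

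The article gives no list sizes, no share of unregistered diagnoses and no weights. No size can be put on a list-based uplift, on differential registration or on a loss of precision from weighting.

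**Conclusion.** The point stands as a contradiction on the primary endpoint, not as missing detail: a fuller document could add to these three statements but could not make them agree. The model and the sample size identify the plain observed proportion as the version that fits the aim.

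The possible consequence is large. On the plan's own detection figures the same trial could give a relative risk of about 1.0, 1.5 or 2.0, depending on how the Abstract phrase is applied. These values assume independent lists, equal true prevalence in the two arms, and 50% and 75% as overall detection. They show how much depends on the wording and do not forecast a bias. The gap between weighted and unweighted results cannot be sized from the article.

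**What to change.** 1. State one primary endpoint in the Abstract, Study endpoints, Analysis of effectiveness, and Primary and secondary endpoints and stratification: the unweighted observed proportion of enrolled contacts with clinically diagnosed TB within 24 months, analysed with the mixed log-binomial model already specified.
2. Remove capture-recapture from the primary endpoint. If only cross-matching of records was meant, say that instead.
3. Report weighted proportions as descriptive estimates, and say that the weights do not enter the primary model.
4. Match all enrolled contacts against the programme's register in the same way in both arms, and add a sensitivity analysis limited to registered cases. Redefining the primary endpoint as registered cases would go further than the defect requires and would depart from clinically diagnosed TB.

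The cost is wording and one additional sensitivity analysis. The sample size is unchanged, because it was calculated for the plain proportion. The article gives the trial as still recruiting, so the change can be made before outcomes are analysed.

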**Discussion:**

The effectiveness of contact investigation as a tool for improved tuberculosis case finding has not been established. This cluster randomized trial will provide valuable operational information for national tuberculosis programs in high-prevalence countries, in order to select the most cost-effective strategies to improve tuberculosis case detection.

**Trial registration:**

The ACT2 study has been registered with the Australian New Zealand Clinical Trials Registry (ACTRN12610000600044).

